### Time Frame for Data Collection

Each participant will receive a short questionnaire at 3 points in time: pretest baseline data (T1), immediately after the intervention (T2), and 8 weeks after the intervention (T3). This self-filled questionnaire will collect data on suicidal ideation, level of suicide literacy, level of confidence, and openness to disclose suicidal ideas to others. The researcher will be responsible for checking for and verifying any missing data with participants, which will help to identify and correct errors in the datasets.

### Data Analysis

Statistical analysis will be conducted using SPSS (version 26; IBM Corp). The normality of data distribution will be assessed, and continuous variables will be summarized using means and SDs (for symmetrical distributions) or medians and IQRs (for skewed distributions), while categorical variables will be presented as frequencies and proportions. Changes in continuous variables (suicidal awareness, suicide literacy, and help seeking) over time will be analyzed using a linear mixed-effects model, and the binary outcome of current suicidal ideation will be analyzed using a population-averaged generalized estimating equation. Linear regression will be used to estimate β coefficients and 95% CIs for predictor variable effects. To compare pre- and postintervention scores on the Literacy of Suicide Scale, a paired samples 2-tailed *t* test will be used, and repeated measures ANOVA with a Bonferroni post hoc test will also be calculated. All primary and exploratory findings will include effect sizes, CIs, and significance levels. While exploratory subgroup analyses may be conducted, they will be clearly identified and interpreted cautiously due to their post hoc nature. Any deviations from the original analysis plan will be justified, and results will be presented with transparency in well-organized tables and figures, including appropriate titles, legends, and footnotes. Data distribution will be further assessed using histograms and the Shapiro-Wilk test to confirm normality assumptions, and the homogeneity of variances will be verified using the Levene test. Any anomalies in the data will be discussed in relation to potential methodological or contextual factors.

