### Research Questions

The primary research question about suicidal ideation is as follows: What is the effect of suicide prevention programs (RAAHI and safeTALK) in reducing suicidal ideation among school-going adolescents in GB?

The secondary research question is as follows: What is the effect of suicide prevention programs (RAAHI and safeTALK) among school-going adolescents in GB on (1) perceived suicidal awareness; (2) perceived Social Support Questionnaire; (3) suicide literacy; (4) attitude toward seeking help related to suicidal ideation; (5) life attitude schedule; (6) depression, anxiety, and stress level; (7) adaptive coping strategies; and (8) self-efficacy.

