### Null Hypotheses

The hypotheses are as follows:

Hypothesis 1—suicidal ideation risk among school-going adolescents in GB is similar at baseline and 8 weeks following the implementation of the suicide prevention program.Hypothesis 2—Compared to baseline, there is no mean difference in suicide awareness, suicide literacy, and attitude to seek help after 8 weeks of participation in a suicide prevention program (RAAHI and safeTALK) among school-going adolescents.Hypothesis 3—Compared to baseline, there is no difference in the mean score of depression, adaptive coping strategies, and self-efficacy after 8-week suicide prevention programs (RAAHI and safeTALK) among school-going adolescents.

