### Study Outcomes

#### Suicidal Ideation

The level of suicide literacy among the participants will be measured through the MSSI by Miller et al [43], comprising 21 items. It was translated and used in Urdu by Bakht et al [51]. The MSSI has shown strong internal consistency, with a Cronbach α coefficient ranging from 0.87 to 0.94 [52]. The severity of suicidal ideation, as assessed by the MSSI total score, is categorized into 3 levels. A total score ranging from 0 to 8 indicates a low level of suicidal ideation. In contrast, a total score between 9 and 20 suggests a moderate level of suicidal ideation. These adolescents may experience more frequent or persistent thoughts of suicide, potentially accompanied by feelings of hopelessness or despair. Finally, a total score of 21 or higher reflects a severe level of suicidal ideation, indicating a significant risk of self-harm or suicide. Adolescents in this category may have intense and intrusive thoughts of ending their life, and immediate intervention and support are often necessary to ensure their safety. Severe suicidal ideation is indicated by a total MSSI score exceeding 20, coupled with an intense suicidal intention, represented by a score of more than 1 on item 7. In addition, an active desire to make an attempt is signaled by a score exceeding 1 on item 3, while a serious plan for suicide is indicated by a score of more than 1 on item 15.

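### The primary outcome is analysed as a yes/no 'current suicidal ideation', but the three-band MSSI scoring is never linked to it, and the severe band is defined in two ways

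*Protocol article*

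**What the plan says.** The Research Questions section makes suicidal ideation the primary question ("The primary research question about suicidal ideation is as follows"). Hypothesis 1 in the Null Hypotheses section states that "suicidal ideation risk among school-going adolescents in GB is similar at baseline and 8 weeks following the implementation of the suicide prevention program", with no threshold. The Data Analysis section then specifies that "the binary outcome of current suicidal ideation will be analyzed using a population-averaged generalized estimating equation". In the same section, suicidal awareness, suicide literacy and help seeking are treated as continuous and go into a linear mixed-effects model.

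The scoring is under Study Outcomes, Suicidal Ideation: "The severity of suicidal ideation, as assessed by the MSSI total score, is categorized into 3 levels". The bands are:

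- Low: "A total score ranging from 0 to 8 indicates a low level of suicidal ideation".
- Moderate: "a total score between 9 and 20 suggests a moderate level of suicidal ideation".
- Severe: "a total score of 21 or higher reflects a severe level of suicidal ideation".

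A few sentences later the same section gives a second description: "Severe suicidal ideation is indicated by a total MSSI score exceeding 20, coupled with an intense suicidal intention". It defines that intention as an item-7 score above 1, and then lists markers based on items 3 and 15. The opening sentence of the section says that the MSSI measures suicide literacy.

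**The concern.** The scoring section sets out a three-level outcome and the analysis section a two-level one, with no rule to get from one to the other. The bands do not supply the rule themselves, because the lowest is worded as a degree of ideation and not as its absence.

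This is the primary outcome of a study with no control group, where the whole result is the change within one cohort. If the cut is chosen after the data are seen, that choice can decide the primary answer. The two severe rules add a further ambiguity, which affects severity reporting in any case and affects the endpoint if severe is the intended cut.

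**Working it through.** The plan states no figure to reproduce, so the check sets the scoring rules against the analysis rule.

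**Step 1: which binary outcomes fit the text.** Inputs are the band edges and the item-7 condition in the Suicidal Ideation section. Whole-number totals and item scores are assumed.

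| Total | Item 7 | Band by total | Yes if ≥9 | Yes if ≥21 | Yes if ≥21 and item 7 >1 |
|---|---|---|---|---|---|
| 6 | 0 | low | no | no | no |
| 12 | 1 | moderate | yes | no | no |
| 25 | 1 | severe | yes | yes | no |
| 25 | 2 | severe | yes | yes | yes |

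The cuts register different changes. A student going from 12 to 6 improves only under the first cut. A student going from 30 to 12 shows no change under the first cut and improves under the second. A student who stays at 25 while item 7 falls from 2 to 1 improves only under the third.

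**Step 2: the two severe rules.** For whole-number totals, 21 or higher and exceeding 20 are the same threshold, so the rules differ only through item 7. A total of 21 or more with item 7 at 0 or 1 is severe by the first rule and not by the second (third row of the table).

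**Step 3: whether another source supplies the yes/no value.** The Pretest Phase section describes a risk assessment that covers current complaints of ideation, but only at pretest. It cannot give the values at T2 and T3 that an analysis over time needs.

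**Step 4: how much the cut could matter (illustration only).** The assumptions, none of which is in the article, are a 25% relative reduction at every cut, a two-sided 5% level, a within-person correlation φ of 0.3 to 0.7, and baseline prevalences of 5% to 40%. The number of pairs is 223, the required sample before dropout in the Sample Size section. With p₂ = 0.75p₁:

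- p₁₁ = p₁p₂ + φ√[p₁(1−p₁)p₂(1−p₂)], b = p₁−p₁₁, c = p₂−p₁₁
- power = Φ{[(b−c)√n − 1.96√(b+c)] / √[(b+c) − (b−c)²]}

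For p₁ = 0.40 and φ = 0.5: p₁₁ = 0.12 + 0.5 × 0.2245 = 0.232, b = 0.168, c = 0.068. Power = Φ[(1.493 − 0.951)/0.475] = Φ(1.14) = 0.87.

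| Baseline prevalence | Power for φ = 0.3 to 0.7 |
|---|---|
| 40% | 75–98% |
| 20% | 38–70% |
| 10% | 20–39% |
| 5% | 12–21% |

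**Step 5: information lost by splitting a score (illustration only).** For a normal score, the relative efficiency of a binary split is φ(z)²/[p(1−p)], where φ(z) is here the normal density at the cut. It is 0.62 at p = 0.40, 0.51 at 0.223 and 0.45 at 0.164. These three rates come from studies cited in the article's Background, and none is tied to an MSSI cut.

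**The case against.** The strongest reply is that three bands and a binary analysis are compatible, since a score can be split at a band edge, and that a cut-off is the kind of detail an analysis plan or full protocol supplies. The article refers to both. Hypothesis 1 speaks of risk, which suits a proportion and a population-averaged model. If many students score at or near zero, a mean score is not obviously the better primary outcome.

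Much of this stands. A reader might infer that the endpoint cannot be derived at all, or that it is constant because even a score of 0 falls in a band called low ideation. The documents do not support either inference: 0–8 can be taken as the reference band, and one stated cut would make the endpoint derivable. A reader might also treat the severe clash as a reason the endpoint fails, but nothing in the article says that severe is the intended cut. The reference to suicide literacy is evidently a slip, because literacy has its own scale and section.

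The appeal to an unseen document does not dispose of the point. The article spends a full paragraph on scoring, down to single items, and that scoring does not connect to the analysis it states. The two severe rules disagree within one section, whatever another document says.

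**Conclusion.** The point holds as a missing link between the stated scoring and the stated analysis of the primary outcome, together with two incompatible rules for severe. At least three binary outcomes fit the text, and they classify the same student, and the same change, differently.

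The consequence for this trial cannot be quantified from the article. The power ranges show only that the choice of cut could matter a great deal under the assumptions listed.

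A reader might also take the 0.45–0.62 efficiencies as this trial's loss of information. They are not. They assume one normally distributed score and borrowed prevalences, whereas the trial has repeated measures on a score that is likely skewed. Splitting the score does lose information, but the amount here is unknown.

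**What to change.** - Analyse the MSSI total score from T1 to T3 in the linear mixed model already planned for the other scales, with a robust or bootstrap confidence interval because the scores are likely skewed.
- Keep the population-averaged GEE on a single binary cut at one of the article's own band edges, written down before the data are examined.
- State which of the two analyses is primary.
- Reconcile the two descriptions of severe so that one rule applies throughout. Which clinical rule applies is for the investigators to decide.
- In the Suicidal Ideation section, replace suicide literacy with suicidal ideation as what the MSSI measures.

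No new data are needed. A mean change in score is less readable than a proportion, which is a reason to keep the binary analysis beside it. The change touches outcomes and analysis, so under the Ethical Considerations section it must be notified to the ethics committee and the registry. Timing matters: the abstract says data collection began in March 2025, while the Results section gives later dates. The amendment should therefore record whether any outcome data had been examined when the cut was fixed.

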### Sampling Strategy

A multicenter experimental study using consecutive sampling will be conducted to examine the effectiveness of school-based preventive interventions for suicidal behavior. Four schools in the GB regions will be recruited. Eligible schools will be randomly selected. Within the selected schools (clusters), all students in grades 9 and 10 will be invited to participate. This approach of inviting all eligible students within the selected clusters aims to enhance representativeness and minimize potential selection bias that could arise if only specific students were chosen from within each school. This is the best technique to explore the phenomena and to gain rich data from the participants [42]. The chosen design enables the detection of trends and changes over time. This method aids in distinguishing intervention effects from other temporal variables to observe whether changes correlate with the intervention time, which strengthens causal inferences. Multiple assessments establish a baseline trend, differentiating natural development from intervention-induced changes [45]. Regular data collection allows for adjustment of external events influencing outcomes. Despite lacking a control group, this approach enables each participant to serve as their own control, enhancing causal inference [46].

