### Sample Size

The sample size for this study was calculated using G*Power (version 3.1.9.2; Heinrich Heine University Düsseldorf) and Microsoft Excel, applying the paired sample formula. Data from the study by Bailey et al [47,48] reported pre- and postintervention knowledge scores with mean values of 16.88 (95% CI 16.17-17.19) and 20.88 (95% CI 20.36-21.41), respectively. To convert the CI into SD, statistical calculations were performed using the standard normal distribution and t-distribution, yielding SD values of approximately 2.2 for preintervention and 1.2 for postintervention scores. With a significance level (α) of .05, power (1–β) of 80%, an estimated effect size of 1.2, and a correlation coefficient of 0.5, the required sample size was determined to be 223 participants. Accounting for a 20% dropout rate [49], the final sample size was adjusted to 267 school-going adolescents to ensure sufficient statistical power for detecting meaningful differences in knowledge scores.

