#### Intervention

The intervention phase consists of 2 workshops in which the students will be required to participate. The first workshop consists of 2 hours of RAAHI intervention which will provide them with general knowledge about suicide, risk factors, consequences, and preventive strategies; this will help participants improve their suicide literacy. Moreover, a booklet comprising different activities will also be provided to participants during the training. In addition, the second session will introduce the 4-hour safeTALK program, which seeks to increase people’s self-awareness and help-seeking behavior while reducing suicidal ideation. This is a culturally relevant program as it applies basic TALK steps and connects the person with suicidal thoughts with suicide first aid help and further community resources. Moreover, a pocket card containing the “suicide alert steps” will also be provided to the participants at the end of the training. In this study, the safeTALK workshops will be delivered to adolescents, approximately 30 students at a time. The researcher, along with a psychologist, will administer this training with the help of translated videos and material in Urdu, which is culturally appropriate and has been modified and adapted from LivingWorks.

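### The paired t test, repeated measures ANOVA and sample-size formula treat students as independent, although they are taught in about 9 workshop groups within 4 schools

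*Protocol article*

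**What the plan says.** **Clustering.** Sampling Strategy names the schools as clusters: "Within the selected schools (clusters), all students in grades 9 and 10 will be invited to participate". Research Setting gives 4 schools. The Intervention section under Phase 2 states that "the safeTALK workshops will be delivered to adolescents, approximately 30 students at a time". The group size for RAAHI is not given.

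**Sample size.** Sample Size reaches 223 students, raised to 267 for 20% dropout, by "applying the paired sample formula". It gives no ICC and no design effect.

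**Analysis.** Data Analysis assigns suicidal awareness, suicide literacy and help seeking to a linear mixed-effects model, and current suicidal ideation to a population-averaged GEE. For the Literacy of Suicide Scale it then adds that "a paired samples 2-tailed *t* test will be used" and that "repeated measures ANOVA with a Bonferroni post hoc test will also be calculated". It does not say which of the three literacy analyses decides. The Abstract names only paired t tests and ANOVA as inferential methods, for knowledge, confidence, willingness to intervene and help seeking.

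**The concern.** Study Design states that there is no control group, so the pre-post change is the whole effect estimate and its standard error carries all the inference. Students in one workshop share the session, the discussion, the day and local events between baseline and follow-up. If average change differs between workshops for such reasons, the students are not independent observations of change. A paired t test or a student-level repeated measures ANOVA then gives standard errors that are too small, intervals that are too narrow and too many false positives.

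Pairing helps only in part. It removes a school or workshop level that is the same before and after. It does not remove workshop-by-time or school-by-time variation.

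**Working it through.** **The plan's own sample size.** The stated inputs are α 0.05, power 80%, effect size 1.2 and correlation 0.5.
- The paired z formula, read as two-sided, gives n = ((1.96 + 0.84)/1.2)² = 5.4, so 6. The exact noncentral-t version gives 8.
- The stated 223 does not reproduce. It would correspond to a standardised change of (1.96 + 0.84)/√223 ≈ 0.19.
- 267 is 223 × 1.2 = 267.6, rounded down.

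The mismatch in 223 is a separate problem. What matters here is that the calculation contains no cluster term.

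**Inputs for the cluster check.**
- Workshops: 267/30 = 8.9, about 9.
- Completers: 267 × 0.8 = 213.6, taken as 213 (20% dropout, from Sample Size).
- Completers per workshop: m = 213/9 = 23.7.
- ICC of the change score: not in the document. Assumed 0.01, 0.02 and 0.05.

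**Formulas.** Design effect DE = 1 + (m − 1) × ICC = 1 + 22.7 × ICC. The interval width factor is √DE. Effective N is 213/DE. The type I error of the nominal 5% test is 2 × (1 − Φ(1.96/√DE)).

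| Assumed ICC of change | DE | Width factor | Effective N | Type I error |
|---|---|---|---|---|
| 0.01 | 1.23 | 1.11 | 174 | 7.7% |
| 0.02 | 1.45 | 1.21 | 147 | 10.4% |
| 0.05 | 2.13 | 1.46 | 100 | 18.0% |

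**Check by simulation.** With 223 students in 9 equal clusters and 10,000 runs, the paired t test rejected in about 8%, 10% and 18% of null trials at the same ICCs, and in 5 to 6% with no clustering.

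**If change varies by school.** The same simulation with 4 clusters gave about 11%, 17% and 31%.

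**If there are more, smaller groups.** Suppose each school splits its roughly 67 students into three groups, giving 12. Then m = 213/12 = 17.75 and DE = 1 + 16.75 × ICC = 1.17, 1.34 and 1.84. The type I error is about 7%, 9% and 15%.

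**Power at the stated effect size.** With groups of 30, DE at ICC 0.10 is 1 + 29 × 0.10 = 3.9. The 8 students needed become 8 × 3.9 = 31.2, so 32. The planned 267 far exceeds that.

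**The case against.** **The ICC of change is assumed.** This stands. If it were zero, the paired test would hold its level. Data Collection also promises identical training for everyone, which limits variation due to delivery. It does not remove shared discussion or local events, so a small positive ICC is plausible, but its size is unknown.

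**The plan already names models that can carry clustering.** This stands in part. Either the mixed model or the GEE could take a workshop or school level. The article states none, and a condensed article may leave that to the SAP, so this silence is not counted as an error. Neither model repairs the t test, the ANOVA or the sample-size formula, which are stated outright.

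**Stronger readings that the document does not support:**
- *The primary result has an inflated false-positive rate.* Suicidal ideation goes to the GEE, whose cluster unit is unstated rather than wrong.
- *The trial is underpowered.* At the stated effect size of 1.2 it is not.
- *The type I error is 8%, 12% and 21%.* Those values need 30 analysed students per workshop, so they hold only if nobody drops out.
- *The three literacy analyses use different subsets.* Data Collection restricts analysis to students who complete the surveys, with intention-to-treat only where feasible. Nothing shows that the subsets differ.
- *The Levene test is misapplied to the ANOVA.* The plan says only that "the homogeneity of variances will be verified using the Levene test" and does not tie it to the ANOVA. The same section plans regression and possible subgroup analyses, where independent groups can exist. The point is minor.

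**Conclusion.** The concern holds for the analyses that the article states. The paired t test, the repeated measures ANOVA and the paired sample-size formula ignore a grouping that the article itself describes. For an ICC of change of 0.01 to 0.05, 9 workshops and 213 completers, type I error is about 8% to 18% instead of 5%, and intervals should be about 11% to 46% wider. School-level variation in change would make this worse; a larger number of smaller groups would lessen it.

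Suicide literacy and the other secondary outcomes in the Abstract are affected directly. The ideation GEE is affected only if it is clustered on student alone. The direction of the error is certain only when the ICC of change is above zero, and its size cannot be fixed from the document.

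**What to change.** 1. Record workshop ID for every student at delivery; it may be hard to reconstruct later.
2. Make the linear mixed model already named in Data Analysis the single analysis for each continuous outcome, literacy included. Use student and workshop random effects, a workshop-by-time random effect, school and school-by-time as fixed effects, and Satterthwaite degrees of freedom. A school main effect alone would not absorb differences between schools in change. State that inference is conditional on these 4 schools.
3. Cluster the ideation GEE on workshop, with school adjustment and a small-sample correction, because about 9 clusters are few.
4. Drop the paired t test and repeated measures ANOVA, or label them supportive. A t test on the workshop mean changes can serve as a check. In a simulation of 9 workshops of 30 it rejected in 4.6%, 4.9% and 5.2% of null trials at ICC 0.01, 0.02 and 0.05. No school-level component was reported for that simulation, so it supports this test as a check only.
5. State the assumed ICC of change and the design effect beside the sample size, and bring the Abstract's list of methods into line.

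The cost is revised wording, one extra field on each form and somewhat wider intervals. With 9 workshops in 4 schools, only about 9 − 4 = 5 degrees of freedom remain for workshop variation within schools.
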